## Abstract

**Background:**

Catheter-related bladder discomfort (CRBD) is a common distressing symptom complex during the postoperative period, especially after urologic procedures with a relatively greater size urinary catheter. In this study, we will enroll male patients undergoing elective prostate surgery with urinary catheterization under general anesthesia, and we will compare the efficacy of pudendal nerve block (PNB) and intravenous tramadol in CRBD prevention.

**Methods/design:**

This trial is a prospective, randomized controlled trial that will test the superiority of bilateral PNB with 0.33 % ropivacaine compared with intravenous tramadol 1.5 mg/kg for CRBD prevention. A total of 94 male patients undergoing elective prostate surgery with urinary catheterization after anesthesia induction will be randomized to receive either bilateral PNB with 0.33 % ropivacaine (the PNB group) or intravenous tramadol 1.5 mg/kg (the tramadol group) after the completion of surgery. The primary outcome is the incidence of CRBD. The most important secondary outcome is the severity of postoperative CRBD, and other secondary outcomes include Numeric Rating Scale (NRS) score for postoperative pain; incidence of postoperative side effects such as postoperative nausea/vomiting, sedation, dizziness, and dry mouth; postoperative requirement for tramadol as a rescue treatment for CRBD and sufentanil as a rescue analgesic for postoperative pain; and NRS score for acceptance of an indwelling urinary catheter.

**Discussion:**

This trial is planned to test the superiority of PNB with 0.33 % ropivacaine compared with intravenous tramadol 1.5 mg/kg. It may provide a basis for a new clinical practice for the prevention of CRBD.

**Trial registration:**

ClinicalTrials.gov identifier NCT02683070. Registered on 11 February 2016.

**Electronic supplementary material:**

The online version of this article (doi:10.1186/s13063-016-1575-y) contains supplementary material, which is available to authorized users.

## Background

Catheter-related bladder discomfort (CRBD) in patients with urinary catheterization during operation is frequently reported in the postanesthesia care unit (PACU) [1]. It is a distressing symptom complex characterized as a burning sensation or stabbing pain with an urge to void or as discomfort from the suprapubic area to the urethra [2]. The condition of CRBD may aggravate postoperative pain, increase the incidence of postoperative complications, and result in prolongation of hospital stay [2–4].

The mechanism of CRBD is mediated by type 3 muscarinic receptor activation, which increases acetylcholine release and then causes the detrusor muscles of the bladder to contract involuntarily [5]. Antimuscarinic agents, including tramadol, tolterodine, oxybutynin, pregabalin, and ketamine, have been applied to treat CRBD in clinical practice [6–10]. However, in spite of their beneficial effect on CRBD, systemic administration of these agents is associated with side effects such as nausea or vomiting, sedation, dizziness, or other unpleasant complications, which may result in reduced quality of recovery. It is important in clinical practice to establish an effective treatment for CRBD with reduced adverse effects.

## Methods/design

### Design

The PNB trial (ClinicalTrials.gov identifier NCT02683070) is an investigator-initiated, prospective, randomized controlled trial that will test the superiority of PNB with 0.33 % ropivacaine to intravenous tramadol 1.5 mg/kg for reduction of CRBD. It will be conducted in accordance with the principles outlined in the Declaration of Helsinki and will follow the Consolidated Standards of Reporting Trials (CONSORT) statement (http://www.consort-statement.org/). A brief flow diagram of the PNB trial is provided in Fig. 1, and a populated Standard Protocol Items: Recommendations for Interventional Trials (SPIRIT) checklist is provided in Additional file 1.

**Fig. 1 Fig1:**
[figure not shown]
The pudendal nerve block trial algorithm

The study has no external financial sponsor, and there are no conflicts of interest in the study design, data collection, analysis, or results interpretation. Before we start the study, all of the participants, including physicians, interns, and nurses, will be educated and trained, and some of them will be responsible for follow-up. After the completion of this trial, the role of the participants, including trial designer, trial executor, and staff responsible for follow-up, will be stated in detail.

### Sample size calculation

The incidence of CRBD has been reported to range from 47 % to 90 % according to different types of surgery, and male sex has been identified to be an independent predictor in previous studies [1, 3]. We investigated 367 male patients in the PACU of the Department of Anesthesiology, West China Hospital, from 21 June 21 to 17 July 2015 and found that 56.1 % (206 of 367) of them complained of CRBD. On the basis of this information, a difference of 25 % (e.g., 30 % vs. 55 %) in the incidence of CRBD values between two treatment groups is considered to be clinically important. The sample size was calculated to compare two proportions with two-sample noninferiority or superiority; assuming the difference between two groups at a 5 % significance level and a power of 0.80, 37 patients in each group are required for a comparison within the groups. Considering an estimated 20 % dropout rate, 47 patients in each group, and 94 patients in total, are required in this study.

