### Statistical analysis

An intention-to-treat analysis will be performed to compare all primary and secondary outcomes with the use of SPSS version 18.0 software (SPSS, Inc., Chicago, IL, USA). Demographic data will be compared using Student’s *t* test. The incidence of CRBD and postoperative side effects will be analyzed by chi-square test. The severity of CRBD will be analyzed using Fisher’s exact test. NRS scores for postoperative pain and acceptance of the indwelling urinary catheter will be analyzed using the Mann-Whitney *U* test. Postoperative tramadol and sufentanil requirements will be analyzed using the *Z* test. *p* < 0.05 will be considered to be statistically significant.

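### The stated 37 patients per group give about 59% power for 30% vs 55% under the planned chi-square test, not 80%; all 94 patients with no dropout give about 69%

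*Protocol article*

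**What the plan says.** The sample size section of the protocol article starts from a survey of male patients in the hospital's own recovery unit, which "found that 56.1 % (206 of 367) of them complained of CRBD". From this it takes "a difference of 25 % (e.g., 30 % vs. 55 %) in the incidence of CRBD values between two treatment groups" as the clinically important effect. It describes the method in one line: "The sample size was calculated to compare two proportions with two-sample noninferiority or superiority". The result is that, "assuming the difference between two groups at a 5 % significance level and a power of 0.80, 37 patients in each group are required". Dropout is then added: "Considering an estimated 20 % dropout rate, 47 patients in each group, and 94 patients in total, are required in this study".

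The section does not say whether the 5% level is one-sided or two-sided, and it gives no margin. The statistical analysis section settles the test: "The incidence of CRBD and postoperative side effects will be analyzed by chi-square test", with p "< 0.05 will be considered to be statistically significant". No one-sided test is mentioned. The abstract, the design section and the discussion all present the trial as a test of superiority of the nerve block over tramadol.

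**The concern.** The section gives both rates, the significance level, the power and the resulting number, so the result can be checked directly. A number as low as 37 is surprising for a 25-point difference centred near 43%, where the binomial variance is close to its maximum. The description of the method does not help, because it names noninferiority and superiority together, while the analysis is an ordinary chi-square test.

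This calculation is the only justification for enrolling 94 patients, and it concerns the single primary outcome. If the stated power is wrong, the trial is much more likely than its readers are told to miss a benefit that the protocol itself calls clinically important. A non-significant result would also be judged against 80% power that the trial does not have.

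**Working it through.** **Inputs** (sample size and statistical analysis sections)
- p1 = 0.30, p2 = 0.55, difference d = 0.25, mean rate 0.425
- significance level 5%, power 0.80 (z = 0.842), equal groups
- chi-square test at p < 0.05, so two-sided (z = 1.960); one-sided (z = 1.645) is shown as a sensitivity check
- margin 0, since none is given and the aim is superiority

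**Building blocks**
- p1(1 − p1) + p2(1 − p2) = 0.2100 + 0.2475 = 0.4575, square root 0.6764
- 2 × 0.425 × 0.575 = 0.48875, square root 0.6991

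**Trying to reproduce 37**

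Unpooled formula, n = (z_α + z_β)² × 0.4575 / d²:
- two-sided: (1.960 + 0.842)² × 0.4575 / 0.0625 = 57.5, so 58
- one-sided: (1.645 + 0.842)² × 0.4575 / 0.0625 = 45.3, so 46

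Pooled formula, which corresponds to the chi-square test, n = (z_α × 0.6991 + z_β × 0.6764)² / d²:
- two-sided: (1.960 × 0.6991 + 0.842 × 0.6764)² / 0.0625 = 60.2, so 61
- one-sided: (1.645 × 0.6991 + 0.842 × 0.6764)² / 0.0625 = 47.3, so 48

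Other variants, per group:

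| Variant | Two-sided | One-sided |
|---|---|---|
| Arcsine, 30% vs 55% | 60 | 48 |
| Continuity-corrected, 30% vs 55% | 68 | 55 |
| Pooled, 31.1% vs 56.1% (25 points below the surveyed rate) | 61 | 48 |
| Pooled, 30% vs 56.1% | 56 | 44 |

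None gives 37. It can be reached only by changing an input to something the protocol does not state. Three examples, all at one-sided 5%:
- 55% vs 27.5%, unpooled: 36.5, so 37
- 30% vs 55% with an allowance of 3 points in favour of the nerve block, unpooled: 36.1, so 37
- 30% vs 55% at 70% power, pooled: 37

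**Dropout step**

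37 / (1 − 0.20) = 46.25, so 47 per group and 94 in total. This reproduces.

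**Power of the planned test, 30% vs 55%**

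Power = Φ[(d√n − z_α × 0.6991) / 0.6764].
- n = 37, two-sided: (0.25 × 6.083 − 1.960 × 0.6991) / 0.6764 = 0.222, power 58.8%
- n = 47, two-sided: (0.25 × 6.856 − 1.960 × 0.6991) / 0.6764 = 0.508, power 69.4%

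Exact binomial enumeration of the uncorrected chi-square test gives 58.2% and 69.2%. With a continuity correction the exact figures are lower still: 48.9% at 37 and about 61% at 47.

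One-sided at 5%, the same formula gives 70.8% at 37 and 79.8% at 47.

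**Difference detectable with 80% power, control rate 55%, two-sided**
- 37 per group: about 31 points (55% vs about 23.5%)
- 47 per group: about 28 points (55% vs about 26.75%)

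**Size needed for the stated claim**
- 58 / 0.8 = 72.5, so 73 randomised per group (unpooled)
- 61 / 0.8 = 76.25, so 77 randomised per group (pooled)

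**The case against.** The strongest reply is that the sample size section never says two-sided, and that procedures labelled noninferiority or superiority are commonly one-sided. On that reading, power is about 71% at 37 per group and about 80% if all 94 patients are evaluable. Most outcomes are collected within six hours of arrival in the recovery unit and the analysis is by intention to treat, so the full 20% loss may be pessimistic.

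Part of this stands. The figure of 69% with all 94 patients depends on a two-sided test, and missing a true benefit about 4 times in 10 assumes the planned dropout occurs; with no dropout it is about 3 in 10. But the reply does not rescue the statement in the protocol. The planned analysis is a chi-square test with no one-sided rule, and a one-sided 5% calculation still needs 46 to 48 evaluable patients, not 37.

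Three smaller points can be made:
- The rates are introduced as an example. They are, however, the only pair given, and a 25-point difference from the surveyed 56.1% needs the same numbers.
- A superiority test needs no explicit margin, so the missing margin is not a separate fault. It matters only because an unstated allowance of about 3 points is one of the few ways to reach 37, and that would not be a superiority test.
- The study organization section calls this a pilot study. The sample size section nevertheless claims 80% power, and the trial is presented as a superiority test throughout.

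**Conclusion.** The concern holds. Under every standard zero-margin calculation, one-sided or two-sided, 37 evaluable patients per group fall short of 80% power for 30% vs 55%. Under the planned two-sided chi-square test the power is about 59% at 37 per group and about 69% at 47 per group with no loss; 61 evaluable per group (58 unpooled) would be needed. These figures assume the stated rates, equal groups and no continuity correction. How 37 was obtained cannot be established from the protocol, and the conclusion does not depend on it.

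**What to change.** Rewrite the sample size paragraph before recruitment starts. Name the same test as in the analysis, remove the mention of noninferiority, and state what the chosen number delivers, for example:

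> Chi-square test for superiority, two-sided 5% level. With 37 evaluable (47 randomised) patients per group, power to detect 55% vs 30% is about 59% (about 69% if no one drops out). With a 55% control rate, 80% power is available for a difference of about 31 points (28 points with no dropout).

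This is a wording change only. It needs no additional patients; its cost is a less favourable power statement.

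If the investigators wish to keep the claim of 80% power for 25 points, the consistent size is 58 to 61 evaluable per group. After 20% dropout that is 73 to 77 randomised per group, or 146 to 154 in total in place of 94. The upper figure matches the pooled variance of the planned chi-square test. If a one-sided 5% test was intended, both sections must say so and justify it, and the number must still rise to 46 to 48 evaluable per group (46 / 0.8 = 57.5, so 58, to 48 / 0.8 = 60 randomised).

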### Recruitment

A total of 94 patients undergoing elective prostate surgery in lithotomy position with urinary catheterization (16-French Foley catheter) while under general anesthesia will be enrolled at West China Hospital of Sichuan University.

### Randomization and blinding

A biostatistician in the Department of Anesthesiology, West China Hospital of Sichuan University, will perform randomization using SAS version 9.1 software (SAS Institute, Cary, NC, USA). For the purpose of blinding, the results of randomization and group allocation will be concealed in a nontransparent envelope and kept by a research assistant. After confirmation of the patient’s enrollment, the investigator will call the research assistant to get the allocated group and intervention by opening the envelope. The investigators, research assistant, and responsible physicians will not be blinded to the treatment assignment, and the patients, staff responsible for follow-up, and statisticians will be blinded to it.

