### Interventions

In the PNB group, bilateral PNB with 30 ml of 0.33 % ropivacaine (15 ml for each side) will be performed after the operation is finished. In the tramadol group, intravenous tramadol 1.5 mg/kg will be administered after the operation is finished.

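### Envelope opening is tied to enrollment rather than to the end of surgery, so unblinded clinicians may know the arm during the anaesthetic and losses before treatment may fall after randomisation

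*Protocol article*

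**What the plan says.** The protocol article, Randomization and blinding, sets one trigger for disclosure: "After confirmation of the patient’s enrollment, the investigator will call the research assistant to get the allocated group and intervention by opening the envelope". The same section states: "The investigators, research assistant, and responsible physicians will not be blinded to the treatment assignment". It adds that "the patients, staff responsible for follow-up, and statisticians will be blinded to it".

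Interventions places both treatments after surgery. In the control arm, "intravenous tramadol 1.5 mg/kg will be administered after the operation is finished"; the nerve block has the same timing. The Discussion adds that the patient is still under general anaesthesia at that moment.

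Three other places bear on the point:
- Sample size calculation raises 37 per group to 47 with the words "Considering an estimated 20 % dropout rate", without saying when or why patients drop out.
- Statistical analysis plans intention-to-treat for all outcomes.
- The Discussion lists the lack of clinician blinding as a limitation and attributes it to the two different routes of administration.

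**The concern.** Nobody needs the allocation until the operation is over, but the stated trigger can be met before it starts. Two things are at stake.

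First, a clinician who knows the arm during surgery could, even unintentionally, give different analgesics or antiemetics. Pain, nausea or vomiting, sedation, sufentanil requirement and bladder discomfort are all trial outcomes, scored from arrival in the PACU, when intraoperative drugs may still be acting. Blinded follow-up staff protect the measurement. They cannot undo a difference in care already given.

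Second, if the envelope is opened early, a patient whose operation is then cancelled or changed is already randomised. Under intention-to-treat that patient is either analysed untreated, which dilutes the contrast, or has no outcome and is missing. Late opening avoids both.

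**Working it through.** **Order of events.**
1. Trigger for opening: enrollment confirmed (Randomization and blinding). No clock time is given.
2. Earliest time the trigger can be met: the criteria under Enrollment criteria are age, planned elective prostate surgery, medical histories, coagulation disorders, allergy and cognition. None needs the end of surgery to be checked, so enrollment can be complete before induction.
3. Time the allocation is needed: after the operation, in both arms (Interventions).
4. Who knows the arm once the envelope is open: investigators, research assistant and responsible physicians.
5. Any statement that delays opening to the end of surgery: none in the text shown.

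Steps 1 to 5 permit knowledge of the arm during the anaesthetic. They do not require it.

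**The plan's dropout figure.** 37 / (1 − 0.20) = 46.25, rounded up to 47 per group. This step reproduces. On 94 patients, 20% is 0.20 × 94 = 18.8, about 19.

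**Power at stake.** The inputs are 55% vs 30% and a 5% level, from Sample size calculation. The level is taken as two-sided, because the section does not say. Late opening adds evaluable patients only if 94 counts opened envelopes. For n evaluable patients per group:

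power = Φ{ [0.25·√n − 1.96·√(2 × 0.425 × 0.575)] / √(0.55 × 0.45 + 0.30 × 0.70) }

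The two constants are 1.96 × √0.48875 = 1.370 and √0.4575 = 0.676.

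- All dropout remains (n = 37): (1.521 − 1.370) / 0.676 = 0.222, power 59%.
- Half of the dropout arises before surgery ends and is avoided (about 9 patients in all, 5 per group, n = 42): (1.620 − 1.370) / 0.676 = 0.370, power 64%.
- All dropout arises before surgery ends and is avoided (n = 47): (1.714 − 1.370) / 0.676 = 0.508, power 69%.

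The gain is therefore 0 points if no dropout arises before surgery ends, about 5 if half does, and about 10 if all does. The share is an assumption, since the documents give none. The calculation treats avoided losses as missing outcomes. Patients analysed untreated would instead dilute the effect, and that is not quantified here.

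The 59% at 37 per group is below the stated 80% because 37 does not reproduce for these rates (61 per group two-sided, 48 one-sided, by the pooled formula). That is a separate matter and does not bear on this point.

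**The case against.** The strongest reply is that the article gives an order, not a time. The abstract's phrase "after the completion of surgery" attaches most naturally to the treatment but could be read as the time of randomisation. Recruitment speaks of patients undergoing surgery, and the trial flow figure is not shown. Opening an envelope after enrollment is ordinary concealment practice, and the exact moment of the call might be left to a fuller protocol. This stands in part: a reader might infer that the envelope is in fact opened before induction, and the documents do not say so. It does not dispose of the point. The article states a trigger, and that trigger can be met hours before the allocation is needed. If the abstract does mean randomisation after surgery, the methods section should say so.

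A reader might also infer that the primary comparison is biased. The documents do not support that. Bias needs intraoperative care to differ by arm, and the article does not describe the anaesthetic regimen. Patients and outcome assessors are blinded, which confines the risk to care given. Clinicians will know the arm from the intervention onward in any case, so late opening removes only the intraoperative part. The declared limitation, being about routes, explains knowledge at delivery and not before it.

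Finally, a reader might take 10 points of power as the expected loss. That needs every dropout to occur before surgery ends. Later loss is equally compatible with the text, since catheter acceptance is scored after catheter removal.

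**Conclusion.** The point holds as a weakness in how the trigger is fixed. The text allows unblinded clinicians to know the arm during the operation and, if they do, places any loss before treatment after randomisation. Neither is shown to happen, and the direction and size of any co-treatment effect are unknown. The power at stake is about 5 points if half of the 20% dropout arises before surgery ends, with a range of 0 to about 10 (two-sided 5% level, 55% vs 30%, avoided losses counted as missing outcomes). The case for change rests mainly on closing an unnecessary route to differential care at almost no cost, and does not depend on the power figure.

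**What to change.** In Randomization and blinding, keep consent and confirmation of eligibility at enrollment, but state that the envelope is opened only when the operation is finished, immediately before the allocated treatment, and that the time of opening is recorded. State also that the randomised set, and so the intention-to-treat set, begins at opening, and that 94 counts opened envelopes. No new eligibility condition is needed.

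The cost is small, since the article reports that recruitment has not begun. The research assistant must be reachable at the end of each operation, and there may be a short wait while the patient is still under anaesthesia. Patients lost before opening are replaced, so somewhat more must consent: under the half assumption, 94 / 0.90 = 104.4, about 105.

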### Study organization

The study will be supervised for data completeness and accuracy by the Department of Anesthesiology, West China Hospital, and RL will be responsible for data monitoring and alerting for serious complications. The data safety and monitoring board will be involved for the duration of the trial. There are no stop rules in this pilot study, and no preliminary analysis will be performed before the completion of this study.

### Enrollment criteria

The following are the inclusion criteria:Male patients aged 18–80 yearsUndergoing elective prostate surgery in lithotomy position with urinary catheterization while under general anesthesia

The exclusion criteria are as follows:History of bladder dysfunction, including overactive bladder, which is defined as urinary frequency more than three times in the night or more than eight times in 24 h [5]; neurogenic bladder; and bladder outflow obstructionCoagulation disordersHistory of vestibular dysfunctionHistory of substance abuseKnown allergy to ropivacaine, tramadol, or any other anesthetic agentHistory of postoperative deliriumImpairment of cognitive function

